**Version 2 22/05/2020 -amended in response to COVID-19 interruption**

**Aims**

This study will test feasibility of LUNA in terms of participant recruitment and retention, and adherence throughout the study (assessment and treatment sessions). We will explore participant acceptability of LUNA and project procedures (satisfaction, perceived benefits, assessment and treatment burden) in semi-structured individual interviews with participants. We will investigate initial efficacy by comparing outcomes on a range of measures across participants who have and have not received LUNA intervention. We will assess treatment fidelity by reviewing a sample of videotaped sessions to check they were delivered as intended by the treatment manual. The study will also test the feasibility and acceptability of remote assessment and treatment delivery. For example, recruitment, retention and compliance data will attempt to identify losses due to technological factors; and interview questions will explicitly probe the experience of using video-conferencing technology. Indicative outcome data will be for remote (not face-to-face) LUNA.

**Methods**

**Design**

The study is a single-blind, waitlist, randomised controlled trial of LUNA for people with chronic post-stroke aphasia. Participants will complete assessments at three time points: T1 (weeks 1&2), T2 (weeks 13 & 14) and T3 (weeks 25 & 26). Following T1, participants will be randomised to an immediate or delayed condition. Those in the immediate condition will receive LUNA therapy between T1 and T2. Those in the delayed condition will receive LUNA therapy between T2 and T3. All participants will be invited to participate in in-depth individual semi-structured interviews post-therapy to explore their experiences of taking part in the study.

In line with our selection criteria, participants will not be receiving any other speech and language therapy during the study. Owing to COVID 19, it is anticipated that most participants will not have access to usual care (attendance at stroke groups). Some may access on-line supports, for example provided by Aphasia Re-Connect. Use of such services is not an exclusion criterion. Use of other services will be explored in the interviews.

We will follow the CONSORT 2010 extension statement to randomised feasibility trials in planning, conducting and reporting on the study <https://www.bmj.com/content/355/bmj.i5239>.

**Ethical approval**

Ethical approval to conduct the study was granted by the School of Health Sciences Research Ethics Committee, City, University of London (ETH1920-0210 on 04/02/2020). The trial sponsor is City, University of London, and the study is funded by the Stroke Association (TSA2017/01). Our funder has formally approved the adapted study (20/05/2020).

**Participants**

***Setting***

Participants will be identified from community stroke support groups across England. Co-ordinators of the stroke groups will be emailed and invited to refer potential participants. The study will also accept self-referrals, from any person with aphasia living in the UK.

***Remote Data Collection***

All recruitment, assessment, treatment and interview sessions will be conducted online using Zoom video conferencing technology. This platform was recommended by our aphasia advisory group and has been used in previous aphasia studies (Dekhtyar et al, 2020). It has been approved for use by our institution (City, University of London) and is widely used by NHS and voluntary sector services. A number of features make this platform suitable for aphasia intervention, including low language demands, a whiteboard facility and screen sharing.

***Inclusion and exclusion criteria***

Inclusion: Participants must be adults (18+ years); diagnosis of ischaemic or haemorrhagic stroke; and have aphasia due to a stroke that occurred at least 12 months prior to recruitment. Participants must be literate and fluent users of English prior to their stroke (self-reported). They must have adequate hearing and vision with aids and glasses, e.g. in order to see pictorial and written assessment and therapy materials. Participants must have access to a computer or tablet and an internet connection. They must be able to download and access Zoom, either independently or with the support of a friend/family member who is living with them.

Exclusion: Participants must not be receiving speech and language therapy elsewhere for the duration of the study. They must not be participating in any other aphasia treatment research project for the duration of the study. Usual stroke supports, for example provided by the voluntary sector, can proceed, although these are likely to be curtailed owing to COVID-19. They must not have severe aphasia, defined as a score of 7 or less on the receptive domains (auditory and reading) and 7 or less on the expressive domains (speaking and writing) of the Frenchay Aphasia Screening Test (FAST: Enderby et al., 1986; unlikely to benefit from treatment). They must not have a secondary cognitive diagnosis such as dementia. This will be established via self-report and/or the confirmation of the referring group co-ordinator and/or by expert clinical judgment of research project staff (experienced therapists).

**Recruitment and consent processes**

Participants will be recruited from voluntary sector community stroke support groups or via self-referral. Researchers will make email and phone contact with group coordinators. Many also attended a project information event in February 2020 held at the university. Members of the research team will provide information to group coordinators and to any individuals enquiring about the project. Coordinators will make direct referrals of individuals (with their Permission) to the research team. The study will also be advertised through the project website via a blog posting (<https://blogs.city.ac.uk/luna>) and social media (project twitter handle @LUNA_Aphasia) will be used to draw attention to the blog posting. Those who are interested in the project will have a 1:1 conversation with a member of the research team to discuss potential eligibility further. A member of the research team will carry out the information and consent process with individuals via Zoom.

We acknowledge that this project is not appropriate for individuals with severe aphasia. We endeavour to attract and screen only individuals with aphasia who are likely to have mild and moderate impairments in their language abilities; and we will not actively advertise the project to individuals with severe aphasia. Firstly, we will manage this sensitively in our communications with community stroke and aphasia group coordinators so that they understand clearly who the project is likely to benefit and who it will not. That is, individuals who find it difficult to say and understand single words would not benefit. Secondly, we will communicate clearly with potentially eligible participants by describing in lay language the kind of language ability profiles for whom this project may benefit and those for whom it won’t. For example, “if you can say and understand single words and sentences most of the time, then this project is for you”; “if saying any words or understanding words is hard, this project is not for you”.

a) Consent will be obtained primarily by the SLT researcher on the project ([name]) but may also be supplemented by members of the research team ([name], [name], [name], [name]) who are based at City and will be involved in recruitment activities as appropriate.

b) Participants will sign 2 copies of the consent form and will keep one.

c) Participants will receive the PIS prior to contact with the researcher. These will be posted and emailed to group coordinators (whose contact details are publicly available on the Stroke Association website). They will identify possible participants from their stroke group and forward the information to them. Individuals who express an interest will be referred by co-ordinators to LUNA. The PIS will also be emailed/posted directly to people with aphasia who make a self-referral.

Interested individuals will meet with a research team member 1:1 (or with family and/or significant other present if preferred by the person with aphasia). The meeting will take place over Zoom. The researcher will go through the PIS (reading it aloud), answer any questions about it, and check the individual’s understanding of the content as well the implications for them. The researcher will go through a simple screening interview and will administer the Frenchay Aphasia Screening Test (Enderby et al., 1986) to check eligibility (project is not suitable for people with severe aphasia). Those who are eligible and interested will be emailed the Consent Form. They will be asked to sign this before their next appointment which will occur at least 24 hours later. The Consent Form can be scanned or posted back to the LUNA team. Participants who are able may also wish to use the annotate function in Zoom to tick and sign the Consent Form which will be saved in electronic format.

d) Participants will have at least 24 hours between receiving information about the study and signing the Consent Form.

Informed consent is recognised as an important matter in this study. PWA do not have cognitive impairment and do not lack capacity as a result of their stroke and aphasia; however, informed consent is mediated through communication (reading printed information, understanding verbal explanations, speaking to question aspects and comment) and as such is more challenging with a language impairment. We have addressed this issue by providing information in an accessible format, following national and international guidance (including Pearl & [name], 2017). Those in the research and treating team are qualified staff who are experienced in communicating with PWA and recruiting individuals, and all new staff involved will receive training in supporting communication so that participants can fully engage throughout the whole research period. The project team has expertise in working remotely with people who have aphasia (see Woolf et al, 2016; [name] et al, under-review).

**Randomisation**

Individuals will be randomized to the immediate or delayed condition by an independent person, blinded to screening results. Participants will be recruited in two cohorts of 12 participants each, starting at different time points so that there is appropriate staffing for the length of the project.

**Blinding**

Participants, the project manager, research speech therapists, the qualitative researcher, and the joint principal investigators will be aware of group allocation. However, the assessors (research assistants) who conduct the language, discourse and psychosocial assessments at all time points will be blinded to group allocation; as well the broader research team (co-investigators). Participants will be requested not to reveal their group allocation to staff during visits and will be reminded of this prior to the visit and at the start of the visit. Visits will be organised by the project manager, and research assistants will have no access to participant files or details. If a research assessor becomes unblinded, this will be reported, and subsequent visits carried out by another assessor. Near misses will also be reported. A log will be kept of all instances of unblinding and near misses, as well as the reason for the unblinding.

**Intervention**

LUNA intervention comprises 20hrs of treatment, 2 sessions per week of 60 minutes each, for 10 weeks. All sessions will be delivered over Zoom. One session is delivered by a qualified speech and language therapist; the other session is delivered by an assistant (student or volunteer) following guidance and under distance supervision. Both therapist and assistant will receive LUNA training. This model of delivery reflects the intended future implementation model in the NHS community setting and was decided by the LUNA Advisory Group. The treatment is specified in the TIDIER checklist (see end of document). In brief, it aims to improve spoken discourse production, using personal narratives as assessment and treatment stimulate, and by integrating word, sentence and discourse level tasks. Treatment is manualised and has been codesigned with key stakeholders (providers and users).

**Outcomes**

Clinical assessments at all three time periods will be conducted by individuals separate from the treating staff who will be blinded to group allocation. All sessions will be delivered over Zoom. Discourse (two personal narratives told at each time point) will be elicited and be analysed following the LUNA protocol. Analysers will be separate from the treatment staff and will also be blinded to group allocation. Interviews will be conducted by an individual trained in qualitative methods and separate from the treating staff. Interviews will follow a topic guide, and also include the 4 item Session Rating Scale as rated by the participant (which invites them to reflect on respect and understanding, relevance of the goals and topics, client-practitioner fit, and overall alliance). Specific questions will also explore the use of video-conferencing technology, for both assessment and therapy, and the degree to which this might have affected treatment acceptability and outcomes. Interviews will be conducted at post-therapy only and in a 3rd session separate from the assessment sessions. A random sample of 10% of treatment sessions will be recorded and observed and checked for adherence to treatment manual and conducted by individuals separate to the treating staff. Recording will be via the Zoom screen recording facility. Participants will give consent for this recording, both on the consent form and (verbally) prior to each recorded session. They will be advised on strategies that protect their privacy (such as background blurring/ replacement).

Data will comprise counts extracted from the screening, recruitment and data collection period (for recruitment (eligibility and consent rates), retention, adherence etc). Data will also comprise qualitative semi-structured interview responses from participants which will be subjected to thematic analysis (Framework). Data will also comprise discourse scores from personal narratives, language assessment scores, and psychosocial questionnaire scores. Assessments and questionnaires have been chosen on the basis that they are psychometrically robust and tested with an aphasic population and have been trialled with 4 PWA on our co-design and advisory group and deemed acceptable. Finally, data will also comprise essential elements deemed to be present or absent from recorded treatment sessions; intra- and inter-rater reliability will also be checked; findings will be assessed using percent agreement across the two raters.

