**Primary endpoints**

1. *Feasibility of recruitment and retention to the trial*: Data will comprise counts/ proportion of those who express interest, are screened and deemed eligible, those who consent, attrition and reasons for attrition if known
2. *Acceptability of the intervention to participants*: Adherence data will be collected (i.e. number/proportion of treatment sessions attended; reasons for non-attendance). Interview data will illuminate participants’ views about the intervention together with scores on the Session Rating Scale (4 items completed within the qualitative interview)
3. *Acceptability of research procedures and outcome measures*: Data will comprise attrition rates and rates of missing data; and qualitative participant interview data on the study experience and procedures

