**Sample size**

This is a feasibility study, so is not powered to provide definitive data about the benefits of the intervention. Our sample size is based on recommended guidance for pilot or feasibility studies i.e. 12 per group (Julious, 2005) and is also the maximum number we can achieve in the time and resources available. We are seeking to recruit 24 participants. Allowing for some attrition this will hopefully ensure that 20 complete the study.

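### The interview and Session Rating Scale part of primary endpoints 2 and 3 is collected only after therapy, so people who withdraw have no stated route to be interviewed

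*Protocol*

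**What the plan says.** The Design section of the protocol sets out who is interviewed and when: "All participants will be invited to participate in in-depth individual semi-structured interviews post-therapy to explore their experiences of taking part in the study". The Outcomes section narrows the timing: "Interviews will be conducted at post-therapy only and in a 3rd session separate from the assessment sessions". It also places the four-item Session Rating Scale, and the questions on video-conferencing, within that interview.

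Under Primary endpoints, endpoint 2 (acceptability of the intervention) has two sources. One is attendance: "Adherence data will be collected (i.e. number/proportion of treatment sessions attended; reasons for non-attendance". The other is the interview: "Interview data will illuminate participants’ views about the intervention together with scores on the Session Rating Scale". Endpoint 3 (acceptability of research procedures and outcome measures) is also mixed, using "attrition rates and rates of missing data; and qualitative participant interview data on the study experience and procedures". Endpoint 1 records "attrition and reasons for attrition if known".

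The delayed arm has its therapy between T2 and T3 (Design). On numbers, the Sample size section plans 24 participants and adds: "Allowing for some attrition this will hopefully ensure that 20 complete the study". No section describes an exit interview or other contact with people who withdraw.

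**The concern.** Acceptability is the subject of two of the three primary endpoints. The Aims section assigns the exploration of satisfaction, perceived benefit and burden to the interviews. Counts can show that someone stopped. They say little about what that person found hard to accept.

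If the interview can take place only after therapy, taking part in it depends on having stayed. People who stop because of the sessions, the assessments, the technology or the wait are plausibly less favourable than those who finish, and they are the ones the interview is likely to miss. The gap is clearest in the delayed arm: someone who leaves during the wait could speak directly to whether waiting was tolerable, yet never arrives at a post-therapy point. Decisions about a future trial would then draw on accounts that come mainly from people for whom the procedures worked.

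**Working it through.** **Does a person who leaves reach an interview under the rule as written?**

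- *Completes therapy, then leaves before T3 (immediate arm).* Has a post-therapy point around T2 and may already have been interviewed.
- *Stops therapy but stays in the study.* Could be interviewed, since the Design section invites all participants, but nothing says what post-therapy means for this person.
- *Withdraws fully during therapy (either arm).* No stated route.
- *Delayed arm, withdraws between T1 and T2.* Therapy has not begun, so there is no post-therapy point.

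**Which data still cover leavers?**

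- Endpoint 1: attrition, with reasons where known.
- Endpoint 2: sessions attended and reasons for non-attendance cover leavers. Interview views and Session Rating Scale scores do not.
- Endpoint 3: attrition and missing-data rates cover leavers. Interview accounts of the study procedures do not.

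The gap is therefore confined to the interview component.

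**How many people could be affected?**

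Inputs from Sample size: 12 per group, 24 recruited, 20 hoped to complete.

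- Planned number: 2 × 12 = 24, which matches the plan.
- Allowance for non-completion: 24 − 20 = 4, and 4/24 = 16.7%.
- Four is an upper figure under that allowance, because completing the study means reaching T3. If, say, 2 of the 4 leave after their interview, the number uninterviewed is 2/24 = 8.3%.

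**How far could the interview picture shift?**

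The protocol defines no proportion finding LUNA acceptable, so this is an illustration only. Let *p* be the favourable share among those interviewed, *q* the share among *d* uninterviewed leavers, and assume everyone else is interviewed. Both shares are assumptions.

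- Share among all 24 = [*p*(24 − *d*) + *qd*]/24.
- Overstatement = *p* − that share = (*p* − *q*) × *d*/24.
- With *d* = 4 the overstatement cannot exceed 4/24 = 16.7 points, and it is zero if *q* = *p*.
- With *d* = 4 and 18 of 20 favourable (90%): if no leaver is favourable, 18/24 = 75.0%; if all are, 22/24 = 91.7%.
- With *d* = 4 and 20 of 20 favourable: between 20/24 = 83.3% and 24/24 = 100%.
- The maximum overstatement is 2/24 = 8.3 points with 2 leavers and 6/24 = 25.0 points with 6.

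**The case against.** The strongest reply is that neither endpoint rests on interviews alone. Attendance, reasons for non-attendance, attrition and missing data all register people who leave, and the Aims section says that recruitment, retention and compliance data will be used to look for losses caused by technology. This stands. A reader might infer that acceptability as a whole is taken from completers, or that leavers are not heard at all. The documents support neither.

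Second, the Design section invites all participants, and the sentence in Outcomes can be read as placing the interview relative to the assessments rather than as an eligibility rule. This stands in part: someone who stops therapy but remains in the study could still be asked. It does not help a person who withdraws fully, and it cannot help a delayed-arm participant who leaves during the wait.

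Third, any percentage is constructed. The interviews are qualitative and analysed by Framework, and no acceptability threshold is set. This stands. Setting 18/20 against 18/24 shows only the worst case in an assumed example, and the four non-completers are an allowance that may include people already interviewed.

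Fourth, a reader might treat the wait as a feature of the full trial. The Quantitative analysis section names usual care as the future comparator, so the importance of the point cannot rest on that.

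Fifth, immediate-arm participants interviewed around T2 would have experienced only two of the three assessment rounds. This is minor: delayed-arm interviews come around T3, and missing data at T3 feed endpoint 3 for both arms.

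**Conclusion.** The concern holds for one component of two multi-source endpoints. Followed as written, the protocol leaves full withdrawals during therapy without a stated route to interview, and withdrawals during the wait without any point at which the interview could occur. The interview and Session Rating Scale evidence therefore risks over-representing completers.

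It goes too far to say that acceptability is biased upward. A favourable tilt is plausible, but it depends on leavers being less favourable than completers, which the documents cannot show. Up to 4 of 24 (16.7%) may be uninterviewed under the protocol's own allowance. In the illustration this bounds any overstatement at 16.7 points, with zero possible. As planned, the trial could not tell where in that range it lies.

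This is more than an omitted detail, because the Outcomes section states the timing as a restriction. It is worth correcting before recruitment, which the Study status section says has not begun.

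**What to change.** 1. In Outcomes, replace the restriction to post-therapy with *post-therapy, or at withdrawal*, and align the invitation sentence in Design.
2. Offer each person who withdraws, including during the wait, a short voluntary exit interview covering technology and assessment burden. Add the Session Rating Scale if the person attended any therapy session.
3. Report the number interviewed out of those randomised, by arm and by completion status, so that readers can see whose views the qualitative findings represent.
4. Optional: repeat a few burden questions after T3 in the immediate arm.

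The cost is a wording change, an ethics note and, under the protocol's allowance, about four short interviews at most, in place of full interviews already planned for the same people. Some leavers will decline, so the gap will shrink rather than close; item 3 makes what remains visible.

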**Secondary endpoints**

1. *Appropriateness of outcome measures*: includes level of variability of scores; missing data; floor and ceiling effects; whether scale constructs align with concepts described by participants during in-depth interviews; and participant in-depth interview on acceptability of measures
2. *Estimating sample size*: based on means and standard deviations and effect sizes of the proposed primary clinical outcome measures (linguistic outcomes, see below) and retention rates.
3. *Assessing treatment fidelity processes*: includes acceptability of fidelity checking processes to participants; utility and reliability of fidelity checklist; extent to which treatment is delivered as intended (as prescribed in the therapy manual)

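### Raw percent agreement is the only statistic named for fidelity-checklist reliability: it ignores chance agreement and gives no measure for the promised intra-rater check

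*Protocol*

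**What the plan says.** Protocol, Secondary endpoints, item 3 (treatment fidelity) includes "utility and reliability of fidelity checklist" and how far therapy was delivered as the manual prescribes. Checklist reliability is therefore a result the study undertakes to report.

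Protocol, Outcomes gives the method. The data are "essential elements deemed to be present or absent from recorded treatment sessions", so each item is binary. The section then promises that "intra- and inter-rater reliability will also be checked" and says that "findings will be assessed using percent agreement across the two raters". No other agreement statistic is named, and no acceptable level of agreement is set.

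On sampling, Outcomes says: "A random sample of 10% of treatment sessions will be recorded and observed and checked for adherence to treatment manual". Checking is "conducted by individuals separate to the treating staff". Participants consent to recording on the consent form and again verbally before each recorded session. No strata are mentioned.

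Protocol, Intervention sets two 60-minute sessions a week for 10 weeks. One weekly session is led by a qualified therapist; "the other session is delivered by an assistant (student or volunteer) following guidance and under distance supervision".

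**The concern.** Two raters who mark most items as present will often agree whether or not they are judging the same thing. Percent agreement counts all of that as reliability. LUNA is manualised and both provider types are trained, so a high share of present ratings is plausible, and that is where percent agreement says least. The same reported figure could describe a checklist that separates good from poor delivery or one that does not.

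Agreement between two raters also says nothing about whether one rater would score the same recording alike twice. The intra-rater check is promised without a measure.

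At stake is whether the checklist can be carried into a full trial. A related question is whether the 10% sample will describe delivery by assistants, since the Intervention section presents the shared therapist and assistant model as the intended NHS one.

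**Working it through.** **Inputs from the Protocol.** 20 hours of therapy as 2 sessions of 60 minutes a week for 10 weeks, half led by assistants (Intervention); 24 participants recruited, 20 hoped to complete (Sample size); a 10% random sample, binary items and percent agreement (Outcomes).

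**Assumptions.** The share of ratings marked present, p, is not given. It is taken from 50% to 95% and as equal for both raters. Observed agreement of 90% is used for illustration.

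**The plan's own figure.** 2 × 10 × 60 minutes = 20 hours, as stated, so 20 sessions per participant, 10 per provider type. With 24 participants: 24 × 20 = 480 sessions, 10% = 48. With 20: 400 and 40. The Protocol gives no reliability figure to reproduce.

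**Agreement beyond chance.** Both coefficients are (Po − Pe)/(1 − Pe), with Po the observed agreement. For kappa, Pe = p² + (1 − p)². For AC1, Pe = 2p(1 − p).

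| p | Pe (kappa) | Kappa at Po = 0.90 | Pe (AC1) | AC1 at Po = 0.90 |
|---|---|---|---|---|
| 50% | 0.50 | 0.80 | 0.50 | 0.80 |
| 70% | 0.58 | 0.76 | 0.42 | 0.83 |
| 80% | 0.68 | 0.69 | 0.32 | 0.85 |
| 90% | 0.82 | 0.44 | 0.18 | 0.88 |
| 95% | 0.905 | -0.05 | 0.095 | 0.89 |

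For p = 90%: kappa = (0.90 − 0.82)/0.18 = 0.44; AC1 = (0.90 − 0.18)/0.82 = 0.88. At p = 95%, each rater marks absent only 5% of the time, so they can disagree on at most 5% + 5% = 10% of items. Observed agreement of 90% is then the lowest possible.

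**Coverage under simple random sampling, 48 of 480.**

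- No session checked for a given participant: C(460,48)/C(480,48) = 0.116; × 24 = about 2.8 participants.
- No assistant-led session checked for a given participant: C(470,48)/C(480,48) = 0.345; × 24 = about 8.3 participants.
- Assistant-led sessions in the sample: mean 24, SD 3.3, 95% range 18 to 30. The chance that either provider type makes up less than 40% of the sample is about 17%.
- With 20 participants (40 of 400), about 2.3 would have no session checked.

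**Does the lack of strata bias overall fidelity?** Assume true fidelity of 0.95 for therapists and 0.75 for assistants. The overall value is 0.5 × 0.95 + 0.5 × 0.75 = 0.85. Over 40,000 simulated unstratified draws of 48 sessions, the sample mean averaged 0.850. There is no bias.

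**The case against.** **The kappa figures depend on an assumed prevalence.** This is correct. At 50% to 80% present, 90% agreement is still a kappa of 0.69 to 0.80. Kappa is also sensitive to extreme prevalence, and AC1 stays between 0.80 and 0.89 over the whole range. The low kappa values do not show that the checklist will be unreliable. They show that percent agreement cannot settle the question, which is why both coefficients and the prevalences are needed.

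**An analysis plan that is not shown could add a chance-corrected coefficient or strata.** This disposes of any complaint that strata are missing: a random 10% does not exclude drawing within provider type, and the Protocol does not promise a check on every participant. It does not dispose of the reliability point, because the Protocol itself names the statistic.

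**Stronger readings that the documents do not support.** A reader might infer that an unstratified sample makes fidelity look better than it is. It does not; a random sample is unbiased for overall fidelity. A reader might infer that providers know which sessions will be checked and perform better in them. Verbal consent before a recorded session makes awareness likely, but the Protocol does not state it and gives no basis for its size. Independent checkers limit rater bias but not a reaction to being recorded. A reader might infer that an unreliable checklist would pass; no pass mark exists. Nor do the documents show that assistants' fidelity is the weaker: assistants are trained, guided and supervised.

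**Conclusion.** The point holds for the reliability statistic. Percent agreement alone can overstate checklist reliability when most elements are present, and it supplies no within-rater measure. Under the assumed prevalences, 90% agreement spans kappa 0.80 to -0.05, with AC1 about 0.88 at 90% prevalence. The true position depends on prevalences that the Protocol does not give, on similar marking rates for the two raters, and on the agreement actually observed.

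The sampling change is an improvement in coverage and by-provider precision, not the correction of an error or a bias. Awareness of recording is a limitation of unknown size.

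The consequence is modest: this is one part of a secondary endpoint in a feasibility study of 24 people, and no primary endpoint rests on it. The change is still worth making because it is nearly free and the Protocol's Study status section says that no data collection has begun.

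**What to change.** **Protocol, Outcomes (reliability).** Beside percent agreement, report Cohen's kappa and Gwet's AC1 with 95% confidence intervals and the prevalence of each element. Do this for the between-rater check and, from repeat scoring by the same rater, for the within-rater check. The cost is a few lines of analysis; the Protocol already promises both checks.

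**Protocol, Outcomes (sampling).** Draw the same 10% as one randomly chosen therapist-led and one randomly chosen assistant-led session per participant, and report fidelity by provider type. If all 24 complete, this is 24 + 24 = 48 of 480 sessions, so the number of sessions to record and rate does not rise.

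**Limitation to state.** Sessions announced as recorded may not represent unrecorded ones. Recording extra sessions and selecting among them afterwards is not recommended here: it would add consent requests and privacy exposure for participants, and the acceptability of fidelity checking is itself part of the same secondary endpoint.
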